#### 2.8.4. Interleukin-6

IL-6 is a reliable marker for predicting neonatal sepsis [27,28]. It is released within 2 h after the onset of bacteremia, reaching its peak at approximately 6 h and subsequently declining over the next 24 h. The accuracy of IL-6 as a predictor is higher in preterm infants compared to that in mixed-study populations. Based on the study by Prinsen et al., the reference interval is calculated as 44 pg/mL [29]. The established cutoff can now be utilized to measure IL-6 as an early pro-inflammatory marker in neonates. Three drops of capillary blood will be collected by neonatal staff for IL-6 levels at birth, at 28 ± 2 days of life, and at 35 ± 1 weeks of PCA, and in any case of suspected neonatal late-onset sepsis. The analyzer’s calibration will be checked with appropriate controls, per product guidelines (POCT model VMFIA1001; BISAF, Wrocław, Poland).

### 2.9. Adverse Events

We will define an adverse event as any unexpected medical incident in an infant, irrespective of a potential causal connection. Every adverse event that takes place from the time of entry into the study until hospital discharge will be documented and recorded. If an adverse event meets the criteria for a serious adverse event (SAE) during this period, it will be reported to the local ethics committee. In the context of this study, a SAE is characterized as any unforeseen medical incident deemed by the investigators to be directly associated with the study intervention, leading to a life-threatening condition, severe or permanent disability, or prolonged hospitalization. SAEs that occur after a participant is removed from the study will not be reported unless investigators suspect a correlation with the study drug or a procedure outlined in the study protocol. The adverse effects of hypervitaminosis of vit D described in the literature are nephrocalcinosis and nephrolithiasis [30,31].

#### 2.9.1. Nephrocalcinosis and Nephrolithiasis

Neonatal staff will collect venous samples (0.7 mL) for the Ca-P metabolism tests, including serum and urine calcium, and creatinine level measurements at 28 ± 2 days of life and at 35 ±1 weeks of PCA. The measurements will be performed using the AU480 chemistry analyzer from Beckman Coulter. The calibration of the analyzer will be verified with suitable controls, following the product guidelines. Hypercalcemia will be defined as a serum level of ≥2.75 mmol/L. Hypercalciuria will be assessed by determining urine calcium-to-creatinine ratios, which vary, depending on the individual’s age [32]. Malone et al. reported that infants born prematurely with lower birth weights and immature kidneys face heightened susceptibility to nephrocalcinosis, the risk factor of smaller kidneys, obstructive hydronephrosis, and hypertension [33]. They observed a trend toward higher average serum 25(OH)D concentrations among preterm infants with nephocalcinosis. The incidence of nephrocalcinosis was high at 41% (23/56) in infants born at ≤32 weeks gestational age. Therefore, monitoring of both the 25(OH)D level and serum and urine calcium levels is recommended in this group of premature neonates. In infants, excess levels of urine calcium and creatinine are considered risk factors for nephrolithiasis. At 35 ± 1 weeks of PCA, infants will undergo a nephrocalcinosis assessment conducted by two independent and skilled ultrasonographers (blinded to the group and other ultrasonographers) using the HD11 XE ultrasound system (Philips Healthcare, Andover, MA, USA). Nephrocalcinosis will be identified by heightened medullary echogenicity, characterized by small white flecks at the tip of the pyramids. Photographic documentation will be captured.

#### 2.9.2. Vit D Intoxication

Vit D intoxication is characterized by a serum 25(OH)D level exceeding 100 ng/mL, leading to hypercalcemia, hypercalciuria, and the suppression of PTH [7]. In cases of vit D overdose treatment, ceasing therapy immediately is crucial. Therefore, calcium levels and urinary calcium excretion should be monitored while also tracking serum 25(OH)D concentrations at 1-month intervals until they reach a level below or equal to 50 ng/mL. Once normocalcemia, normocalciuria, and 25(OH)D concentrations below or equal to 50 ng/mL are achieved, resuming prophylactic or therapeutic interventions can be considered, provided that vit D hypersensitivity has been ruled out.

### 2.10. Retention of Participants in the Study

Given that a significant portion of the enrolled patients require long-term hospitalization, our primary focus will be on effective staff training and ensuring the trial is well-managed by the study team. To address any concerns arising during the trial, we will organize monthly departmental meetings.

### 2.11. Data Monitoring

We opted not to establish a data monitoring committee since the intervention in the trial (i.e., vit D supplementation of 250–1000 IU/day) aligns with the standard of care supported by multiple pediatric societies [7,13,14]. Moreover, we are well-informed about the potential adverse effects associated with this intervention.

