Scientific societies unanimously recommend vit D supplementation in neonatal patients, as well as in pregnant women. The guidelines from the American Academy of Pediatrics (2013) suggest supplementation of 200–400 IU/day (depending on the weight) for enterally fed preterm infants [13]. In line with the latest recommendations from the European Society for Paediatric Gastroenterology, Hepatology, and Nutrition, vit D supplementation for preterm infants should range from 400 to 700 IU/kg/day, with a maximum daily dose capped at 1000 IU/day [14]. The argument for a higher dosage is the prevalence of a commonly occurring deficiency in pregnant women. In addition, the effect on the pleiotropic action of vit D in infants is observed at a concentration of 25(OH)D >30 ng/mL [7,14]. According to Polish guidelines, for neonates born at <33 weeks of gestation, if enteral nutrition is feasible, a dosage of 800 IU/day (20 µg/day) of cholecalciferol is recommended during the initial month of life, irrespective of the feeding method [7]. Dietary intake calculations should commence in the second month of life. Monitoring of supplementation is advised through serum 25(OH)D concentration assays, conducted during hospitalization (with the initial assessment after 4 weeks of supplementation) and/or follow-up in outpatient care. Caution is advised as a total daily cholecalciferol dose >1000 IU (i.e., 25 µg/day) may pose a risk of vit D overdose, particularly in neonates with a birth weight <1000 g.

A previous study [15] conducted in the Department of Neonatology and Neonatal Intensive Care at the Medical University of Warsaw (Warsaw, Poland) showed that approximately 45% of patients had suboptimal and deficiency levels at 4 weeks of age on the initial supplementation of 500 IU. Infants were randomized to receive monitored supplementation (with the option of dose modification, based on 25(OH)D levels, as per protocol) or to receive standard therapy (i.e., 500 IU) for up to 52 weeks of postconceptional age (PCA). However, monitoring has been proven to avoid overdosing during further follow-up. The quantitative ultrasonography assessment of average bone mass did not differ between the two groups of patients, but the initial dose was the same in both groups.

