### 2.6. Intervention

Enrollment will occur within 48 h from birth, typically within the first 24 h of life. During this process, patients will undergo screening for both inclusion and exclusion criteria.

Infants in the monitored group will receive an initial dose of 1000 IU of vit D (cholecalciferol/Devikap; Polpharma, Starogard Gdański, Poland), whereas infants in the controlled group will receive 250 IU for extremely low birth weight infants and 500 IU for infants weighing above 1000 g. The administration of vit D will occur just before feeding via an orogastric tube, until the infants commence bottle feeding directly by mouth. Parenteral nutrition includes an additional 160 IU/kg of vit D, and enteral nutrition comprises 150–300 IU/kg, depending on the quantity and source of enteral feeding (e.g., human milk fortifiers or milk formula). At 28 ± 2 days of age, blood samples will be obtained for 25(OH)D concentration measurement, followed by measurements every 4 weeks and/or 35 ± 1 weeks of PCA. In the monitored group, vit D doses will be adjusted accordingly based on the 25(OH)D levels, following the scheme outlined in the Polish recommendation (Table 2) [7]. Dietary intake will be calculated starting in the 2nd month of life.

Infants assigned to the standard therapy group will undergo the same blood sample collection procedure as the monitored group, but without any alterations in their dosing regimen. If we observe a potentially toxic level of >100 ng/mL, we will stop supplementation in both groups for ethical reasons.

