**Assessment**					
	**First 48 h** **of Life**	**First 48 h** **of Life**	**4 Weeks of Age**	**8 Weeks of Age ***	**35 ± 2 Weeks** **of PCA**
Blood sample for 25(OH)D		X	X	X	X
Blood sample for PTH		X	X	X	X
Blood sample for IL-6		X	**	**	X
Sample collection for Ca/P metabolism			X	X	X
Renal ultrasound					X
Bone mass assessment					X
Adverse events		X ***	X ***	X ***	X ***

25(OH)D: 25-hydroxyvitamin D; PCA: postconceptional age; IL-6: interleukin 6; Ca/P: calcium/phosphorus; IL-6: interleukin-6. * Eight weeks postconceptional age, only for infants born before 26 weeks of gestation. ** Blood sample for IL-6 will be obtained; for a suspected case of late-onset sepsis, a bacteriological blood test will be conducted simultaneously, using a blood sample of at least 1 mL. *** Adverse events monitored from enrollment until hospital discharge.

**Table 2 nutrients-16-00700-t002:** Dosage change, depending on 25(OH)D serum concentration, based on Polish guidelines.

Rules of Vitamin D Supplementation						
Serum concentration of 25(OH)D	<20 ng/mL	20–30 ng/mL	30–50 ng/mL	50–75 ng/mL	>75 ng/mL	>100 ng/mL
Management	Increase supply by 100%	Increase supply by 50%	Maintain the current supply	Reduce the dose by 50%	No supplementation for 1–2 months, and then 50% of the previous dose	Stop supplementation, Assess calcemia and calcuria, consider resuming supplementation after reaching 25(OH)D concentration < 50 ng/mL with normocalcemia and normocalcuria

25(OH)D: 25-hydroxyvitamin D.

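### The 250–1000 IU/day range that section 2.11 uses to justify having no data monitoring committee covers only the starting doses; one upward step in Table 2 takes a monitored infant to 1500 or 2000 IU/day

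*Protocol article*

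**What the plan says.** Five places in the protocol article bear on this.

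- **Section 2.11 (Data Monitoring)** explains the absence of a committee by saying that "vit D supplementation of 250–1000 IU/day) aligns with the standard of care", citing references 7, 13 and 14. It adds a second reason: the team knows the possible adverse effects.
- **Section 2.6 (Intervention)** sets the starting doses. For the monitored arm, "Infants in the monitored group will receive an initial dose of 1000 IU of vit D". The control arm gets "250 IU for extremely low birth weight infants and 500 IU for infants weighing above 1000 g". Only the monitored arm has its dose adjusted, following Table 2.
- **Table 2**, attributed to the Polish guideline (reference 7), tells staff to "Increase supply by 100" per cent below 20 ng/mL and by 50% at 20–30 ng/mL. It also reduces the dose from 50 ng/mL and suspends it above 75 ng/mL. It states no upper limit on the dose.
- **Section 2.6, on nutrition:** "Parenteral nutrition includes an additional 160 IU/kg of vit D", and enteral feeds supply 150–300 IU/kg depending on volume and source. Dietary intake enters the calculation only from the second month.
- **Section 1 (Introduction)** describes one cited guideline as giving 400–700 IU/kg/day "with a maximum daily dose capped at 1000 IU/day". It also says "Caution is advised as a total daily cholecalciferol dose >1000 IU" may carry an overdose risk, particularly at birth weights below 1000 g.

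**The concern.** Dose modification is what defines the monitored arm, yet the range that section 2.11 presents as the intervention leaves it out. The arm begins at the top of that range, so every upward adjustment leaves it. A decision about safety oversight in very preterm infants therefore rests mainly on a dose description that the protocol's own scheme does not meet. The same document flags total intakes above 1000 IU/day as a matter for caution and does not say how this fits with Table 2 or with the nutrition figures. An ethics committee reading section 2.11 alone would take 1000 IU/day to be the maximum.

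The primary endpoint is not affected. It is measured at 28 ± 2 days, on the sample that leads to the first adjustment.

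**Working it through.** **Inputs.** Starting doses of 250, 500 and 1000 IU, and nutrition of 150–300 IU/kg enteral (section 2.6). Multipliers of 1.5 and 2 (Table 2). Control rate 80%, decrease 25%, power 80%, α = 0.05, 54 per group, 130 in total (section 2.12). Body weights of 0.6–2.0 kg are my assumption.

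**1. Reproduce the stated range.** The lowest starting dose is 250 IU and the highest is 1000 IU. The range in section 2.11 is therefore exactly the span of the starting doses.

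**2. Apply Table 2 once, from 1000 IU.**

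| 25(OH)D, ng/mL | Calculation | Supplement, IU/day |
|---|---|---|
| <20 | 1000 × 2 | 2000 |
| 20–30 | 1000 × 1.5 | 1500 |
| 30–50 | unchanged | 1000 |
| 50–75 | 1000 × 0.5 | 500 |
| >75 | suspended | 0 |

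The lower end of the range also fails, because the scheme allows no supplement at all. With no cap stated, a second increase at a later sample would give between 1500 × 1.5 = 2250 and 2000 × 2 = 4000 IU/day.

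**3. How often an increase would occur.** First, which rate does the sample size imply? With the usual two-sided normal formula for two proportions and no continuity correction, 80% versus 55% gives 54 per group, as stated. A relative reading (80% versus 60%) gives 82. The design rate in the monitored arm is therefore 80 − 25 = 55% below 30 ng/mL, and all of these infants would have their dose raised.

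- 0.55 × 54 = 29.7, about 30 infants.
- 0.55 × 65 = 35.8, about 36 infants, if all 130 are randomized equally.
- For an assumed range of 20–60%: 0.20 × 54 = 10.8 to 0.60 × 54 = 32.4, about 11 to 32 infants. The 20% is what a 25-point fall would leave if the control rate were the 45% that section 2.12 reports from the earlier study. The protocol does not state it.

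**4. Total intake at the starting dose.** Total = 1000 + weight × (150 to 300), with the full nutrition content:

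| Assumed weight, kg | Total, IU/day |
|---|---|
| 0.6 | 1090–1180 |
| 0.8 | 1120–1240 |
| 1.0 | 1150–1300 |
| 1.5 | 1225–1450 |
| 2.0 | 1300–1600 |

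Dosing begins at 30 mL/kg/day of enteral feed (section 2.2), when the enteral contribution may be below these figures. The sign does not depend on this: any vitamin D in the feeds, added to 1000 IU, exceeds 1000 IU.

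**5. Try the readings that could rescue the text.** If the range means supplement only, step 4 does not contradict section 2.11, but step 2 still gives 1500–2000 IU/day. If supply in Table 2 means total intake including diet, an increase from at least 1000 IU gives at least 1.5 × 1000 = 1500 IU/day. If the range means initial doses only, the numbers agree, but section 2.11 says it is describing the trial intervention.

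**The case against.** The best defence is that the waiver rests on guideline alignment, not on a number. Table 2 is attributed to reference 7, which section 2.11 also cites, so the increases may themselves be guideline care. This stands as far as it goes. The source is not at hand, and nothing here shows that the increases depart from it. It does not make the stated range correct, and it leaves the Introduction's caution above 1000 IU unreconciled.

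The nutrition argument is the weaker limb, and the objection to it largely stands. Section 2.11 speaks of supplementation, which dietary vitamin D does not contradict, and leaving diet out in the first month follows the convention that the Introduction describes. Diet counts only against the caution, which is worded for the total daily dose.

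A reader might also infer more than the documents support:

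- *That the dose range is the only reason given.* Section 2.11 gives a second one, familiarity with the adverse effects.
- *That there is no safety oversight.* There are dose-reduction and stopping rules (Table 2, section 2.6), serum and urine calcium tests and blinded renal ultrasound (section 2.9.1), and serious adverse event reports to the ethics committee (section 2.9).
- *That 25(OH)D is first measured at day 28.* It is also measured within 48 hours of birth. Day 28 is the first scheduled check after dosing starts.
- *That total intake per kg can be set against 400–700 IU/kg/day.* The Introduction gives that figure for supplementation. The like-for-like value at an assumed 0.8 kg is 1000/0.8 = 1250 IU/kg/day.
- *That a committee is required.* This is a design judgement, and the documents do not settle it.

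**Conclusion.** The point holds as a contradiction within the protocol. The range in section 2.11 describes starting doses but is presented as the intervention, and it is the main support for a decision on safety oversight. One Table 2 step gives 1500 or 2000 IU/day. At the design rate this would apply to about 30 of 54 monitored infants at day 28, or about 11 to 32 if the share below 30 ng/mL were 20–60%. Those counts rest on the absolute reading of the 25% decrease, which the stated sample size supports, and on 55% as an effect to detect. The contradiction does not depend on the counts: one infant below 30 ng/mL is enough.

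The excess of total intake over 1000 IU/day is secondary. Its direction is certain for any infant who takes the 1000 IU dose with feeds containing vitamin D, but its size depends on weight, feed volume and feed source.

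The safeguards and the guideline attribution of Table 2 limit what follows from this. They do not correct the statement. It cannot be concluded that the scheme is unsafe or that any particular dose is wrong.

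**What to change.** 1. Reconcile the Introduction's caution and the cited cap, the doses and nutrition figures in section 2.6, the range in section 2.11, and Table 2. The clinical team must decide which dosing rule stands; no dose is proposed here.
2. Replace the range in section 2.11 with the one the scheme can produce, including reductions, suspension and repeated increases. Give it for the supplement alone and for the total with diet, per infant and per kg, and say whether the total is meant to stay within the limit cited in the Introduction.
3. Re-justify or retake the oversight decision on that range, naming the safeguards relied on. If the argument is that Table 2 is itself guideline care, say so and address the caution above 1000 IU directly.

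The cost is protocol wording and an ethics committee notification. The sample size, the primary endpoint and its analysis do not change.

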### 2.12. Sample Size Calculations

The sample size was determined based on the primary outcome, which is defined as the count of neonates with 25(OH)D deficiency or insufficiency. A previous study conducted in our department reported an incidence of vit D deficiency or vit D insufficiency of 80% in preterm infants at birth, which was reduced with vit D supplementation to 45% at 28 ± 2 days of age. Assuming an estimated prevalence of 80% in the standard supplementation group, we chose to detect a decrease of 25% in patients with vitamin D deficiency and vitamin D insufficiency versus the control group with a power of 80% and α = 0.05 to meet acceptable recruitment rates and reach statistically significant results. Hence, 54 infants are required in each study group. Assuming a 20% loss to follow-up (due to the decision of the principal investigator, withdrawal of consent from a parent/legal guardian), the sample size has been set at 130 patients and their mothers. We believe the recruitment of patients will last approximately 3 years.

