### 2.7. Primary Outcome

The percentage of infants with deficient or suboptimal 25(OH)D levels at 28 ± 2 days of age will be the primary endpoint. The 25(OH)D levels will additionally be measured at 35 ± 1 weeks of PCA. Neonatal staff will obtain venous samples of 0.3 mL to assess the 25(OH)D serum concentration. The study site will utilize the VIDAS automated quantitative test (bioMérieux, Marcy l’Etoile, France) to measure 25(OH)D concentrations. In Poland, the diagnostic thresholds for serum 25(OH)D concentrations are as follows [7]: <20 ng/mL (50 nmol/L) indicates vitamin D deficiency;
>20 ng/mL (50 nmol/L) and <30 ng/mL (75 nmol/L);≥30 ng/mL (75 nmol/L) up to 50 ng/mL (125 nmol/L) reflect adequate to optimal vitamin D status;>50 ng/mL (125 nmol/L) up to 100 ng/mL (250 nmol/L) indicate a high vitamin D supply;>100 ng/mL (250 nmol/L) reflect an increased risk for intoxication [7].

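### The sample size takes the at-birth rate (80%) as the control rate for a 28-day endpoint that the protocol puts at 45%, so the stated detectable effect is the wrong one, although the number per group barely depends on it

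*Protocol article*

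**What the plan says.** Section 2.7 sets the primary endpoint: "The percentage of infants with deficient or suboptimal 25(OH)D levels at 28 ± 2 days of age will be the primary endpoint".

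Section 2.12 draws on an earlier study in the same department. Before supplementation that study found "vit D deficiency or vit D insufficiency of 80% in preterm infants at birth". For the time at which the primary endpoint is read, the section gives a much lower figure: "which was reduced with vit D supplementation to 45% at 28 ± 2 days of age". The next sentence then sets the design: "Assuming an estimated prevalence of 80% in the standard supplementation group, we chose to detect a decrease of 25" per cent, with 80% power and α = 0.05, leading to 54 infants per group. It does not say whether the decrease is absolute or relative.

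The Introduction ties the 28-day figure to a dose: "approximately 45% of patients had suboptimal and deficiency levels at 4 weeks of age on the initial supplementation of 500 IU". It adds that both groups of that study began on the same dose.

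Section 2.6 sets the control regimen here: "infants in the controlled group will receive 250 IU for extremely low birth weight infants and 500 IU for infants weighing above 1000 g".

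**The concern.** The control rate in a sample size calculation should be the rate expected in control infants when the endpoint is measured. Here that time is about four weeks of age, after supplementation has begun. The figure used is the rate at birth, before any supplementation. The sentence just before it reports a much lower rate at the right time, and no reason is given for setting that aside.

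The result is a target that makes no sense as written. A 25-point fall from 80% gives 55% in the monitored arm. The department has already seen 45% on 500 IU, so the monitored arm could reach its planned rate and still do worse than that.

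At stake is the meaning of the detectable effect. A reader of the protocol would take the trial to be sized for a relative reduction of about a third. If the control rate is near 45%, it is sized for a reduction of more than half, and a non-significant result would have to be read in that light.

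**Working it through.** **Inputs.** Endpoint at 28 ± 2 days (section 2.7). Rates of 80% at birth and 45% at 28 ± 2 days, a decrease of 25%, 80% power, α = 0.05 and 54 per group (section 2.12). 1:1 allocation (section 2.5). Two-sided testing is my assumption; it reproduces the stated number.

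**Formula.** Pooled variance, no continuity correction, with d = p1 − p2, q = 1 − p and p̄ = (p1 + p2)/2:

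n = [1.96·√(2p̄q̄) + 0.8416·√(p1q1 + p2q2)]² / d²

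power = Φ{ [d·√n − 1.96·√(2p̄q̄)] / √(p1q1 + p2q2) }

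**Step 1: the plan's figure.** For 80% against 55%, p̄ = 0.675, 2p̄q̄ = 0.43875 and p1q1 + p2q2 = 0.16 + 0.2475 = 0.4075.

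n = (1.96 × 0.6624 + 0.8416 × 0.6384)² / 0.0625 = (1.2983 + 0.5372)² / 0.0625 = 53.9, so **54**. This matches.

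Reading the decrease as relative gives 80% against 60%:

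n = (1.96 × 0.6481 + 0.8416 × 0.6325)² / 0.04 = 81.2, so 82. This does not match. The plan therefore used 25 percentage points.

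**Step 2: same drop from the 28-day rate.** For 45% against 20%, p̄ = 0.325, 2p̄q̄ = 0.43875 and p1q1 + p2q2 = 0.2475 + 0.16 = 0.4075. Every term equals that in step 1, because 45/20 are the complements of 55/80. So n = 54 again, with power 80.1%.

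**Step 3: what the effect means.** Relative reduction for 80% to 55%: 25/80 = 31%. For 45% to 20%: 25/45 = 56%. Solving the power formula for 80% at 54 per group from a 45% control rate gives a monitored-arm rate of 20.0%.

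**Step 4: other rates at 54 per group.**

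| Control | Monitored | Difference (points) | Power at 54 | n per group for 80% |
|---|---|---|---|---|
| 45% | 20% | 25 | 80% | 54 |
| 50% | 25% | 25 | 77% | 58 |
| 55% | 30% | 25 | 75.5% | 61 |
| 60% | 35% | 25 | 74.6% | 62 |
| 65% | 40% | 25 | 74.6% | 62 |
| 80% | 55% | 25 | 80% | 54 |
| 45% | 25% | 20 | 59% | 89 |
| 45% | 30% | 15 | 36% | 163 |

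Example, 45% against 25%: (0.20 × 7.3485 − 1.96 × 0.6745) / 0.6595 = 0.224, and Φ(0.224) = 0.589.

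**The case against.** The strongest reply is that the error hardly touches the sample size. The plan used an absolute difference, and a 25-point drop needs 54 to 62 per group at any control rate from 45% to 80%. Power at 54 stays between about 75% and 80%. This stands, and it limits the point.

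A reader might infer that the trial is badly underpowered. Holding the relative reduction of 31% from a 45% control rate (45% to 30.9%) would give 32% power and need 186 per group; a relative 25% (45% to 33.75%) would give 22% and need 295. The documents do not support that inference. The stated 54 rules out a relative 25%, and the 31% is only a conversion of the absolute target. No relative effect is planned.

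A second reply is that 45% may be too low. It was seen on an initial 500 IU, whereas extremely low birth weight controls here receive 250 IU. This also stands as far as it goes: the share of such infants is not stated, so a range is needed. It does not rescue 80%. Suppose controls above 1000 g run at 45% and, as an extreme, every smaller control is deficient or insufficient. An overall 80% would then need a share s with 45 + 55s = 80, so s = 35/55 = 64%. Section 2.12 does not argue from the lower dose.

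A third reply is that the arithmetic is right. It is; the fault lies in the input. The absolute reading of the decrease can be recovered from the 54, so that ambiguity is a matter of wording.

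**Conclusion.** The point holds as an error in the design assumption. The control rate is a birth figure applied to a 28-day endpoint, it conflicts with the 45% in the same paragraph and in the Introduction, and no reason is given. The effect as stated, 80% to 55%, does not describe the comparison this trial will make.

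It does not follow that 54 per group is wrong or that the stated power is lost. For a 25-point difference, power is 80% at a 45% control rate and about 75% at 60%. What is lost is the modest-looking target: from 45%, 80% power requires about 20% in the monitored arm, and no document supports that rate. Differences of 20 and 15 points from 45% have 59% and 36% power.

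These figures assume a two-sided 5% test, the pooled formula and 54 evaluable infants per group. The upper end of the control-rate range, about 60%, is an assumption. The statement should be corrected before results are interpreted against it.

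**What to change.** In section 2.12:

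- Replace the 80% with a control rate based on 28-day data: 45% as seen on 500 IU, with a range up to about 60%. Label the upper end as an assumption, made because extremely low birth weight controls receive 250 IU and their share is not stated.
- Write 25 percentage points, and state that the test is two-sided if that is intended.
- State that 54 per group gives about 75% to 80% power for that difference over this range.
- Give the implied monitored-arm rate (20% from 45%, a 56% relative reduction) as the detectable effect. The sponsor should justify why it is attainable. It should not be entered as an expected value, since it is obtained by working back from 54 per group.
- Add the power for 45% against 25% (59%) and 45% against 30% (36%).

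The cost is protocol wording and no extra patients. The detectable effect will look less favourable in relative terms. If the sponsor cannot justify a drop of 25 points, the last item shows what a smaller effect would mean for this sample.

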### 2.4. Exclusion Criteria

We will exclude infants born at >32 weeks of gestation and with major congenital abnormalities or other severe congenital malformations, infants with genetic disorders (diagnosed before and after birth) deemed incompatible with survival, and infants with diagnosed cholestasis. Cholestasis is defined as direct bilirubin > 1 mg/dL (>17.1 μmol/L) [20]. Exclusion criteria also include the lack of written informed consent and communication challenges with caregivers.

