### 2.13. Statistical Analysis

Statistical analysis will be conducted using Statistica 13.1 (StatSoft, Tulsa, OK, USA). Our intention is to conduct intention-to-treat analyses. Continuous data will be presented as means and standard deviations or as medians and ranges, while categorical variables will be expressed as proportions. Normally distributed continuous variables will undergo analysis using the Student’s *t*-test, while the Wilcoxon rank-sum test will be applied for skewed data. Categorical variables will be analyzed using either the chi-square test or Fisher’s exact test. The 95% confidence intervals (95% CIs) will be calculated for relative risk, as well as risk differences for categorical variables, and mean differences with 95% CIs will be calculated for continuous variables. We plan to analyze the partial data once annually during the recruitment of patients.

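### The recruitment target of 130 was reached by multiplying 108 by 1.2 instead of dividing by 0.8, so it covers about 17% loss, not the stated 20%

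*Protocol article*

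**What the plan says.** Section 2.12 (Sample Size Calculations) of the protocol article builds the target in three steps.

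- **Design values.** It starts from a control-group rate of 80% ("Assuming an estimated prevalence of 80% in the standard supplementation group"), a 25% decrease from that rate, and the error rates "with a power of 80% and α = 0.05".
- **Evaluable number.** From these it concludes: "Hence, 54 infants are required in each study group".
- **Inflation.** It then allows for attrition ("Assuming a 20% loss to follow-up (due to the decision of the principal investigator", with parental withdrawal of consent as the other named cause) and states that "the sample size has been set at 130 patients and their mothers".

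Section 2.5 gives 1:1 allocation. Section 2.13 names the chi-square test or Fisher's exact test for categorical outcomes and states the analysis principle: "Our intention is to conduct intention-to-treat analyses".

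**The concern.** The evaluable number, the loss rate and the final target stand in consecutive sentences and should agree. They do not. A loss rate applies to the infants randomised, so the evaluable number has to be divided by one minus that rate. Multiplying by one plus the rate gives too few infants.

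The 54 per group is the smallest whole number that reaches 80% power under the stated assumptions, so it holds no slack to absorb a shortfall. If loss reaches the planned 20%, the trial misses both its own required number and its stated power.

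**Working it through.** **Inputs (Section 2.12 unless noted).** Control rate p1 = 0.80. Decrease of 25%, read as percentage points, so p2 = 0.55. α = 0.05, power 80%, loss 20%, allocation 1:1 (Section 2.5). Sidedness is not stated; two-sided is assumed.

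**Step 1: reproduce the 54.** Normal approximation with pooled variance under the null and no continuity correction:

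n = [z(α/2)·√(2·p̄·q̄) + z(β)·√(p1q1 + p2q2)]² / (p1 − p2)²

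- p̄ = 0.675 and q̄ = 0.325, so √(2 × 0.675 × 0.325) = 0.6624
- √(0.16 + 0.2475) = 0.6384
- n = (1.960 × 0.6624 + 0.8416 × 0.6384)² / 0.25² = (1.2982 + 0.5373)² / 0.0625 = 53.9, rounded up to **54 per arm**, 108 in all

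This matches the plan and supports the readings assumed above. A one-sided test would give 43 per arm, and a relative 25% reduction (80% versus 60%) would give 82.

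**Step 2: reproduce the 130.**

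| Method | Calculation | Total |
|---|---|---|
| Multiply by 1 + loss | 108 × 1.2 = 129.6 | 130 (the stated target) |
| Divide by 1 − loss | 108 / 0.8 | 135 |
| Divide, by arm | 54 / 0.8 = 67.5, so 68 per arm | 136 |

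Only the first line gives the stated figure.

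**Step 3: what 130 delivers.**

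- At 20% loss: 130 × 0.8 = 104, or 52 per arm, which is 4 short of 108.
- Largest loss that still leaves 108: 1 − 108/130 = 22/130 = 16.9%.

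**Step 4: power at 52 per arm.** Inverting the formula of Step 1:

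Power = Φ{[0.25·√n − 1.2982] / 0.6384}

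- n = 54: (1.8371 − 1.2982) / 0.6384 = 0.844, power **80.1%**
- n = 52: (1.8028 − 1.2982) / 0.6384 = 0.790, power **78.5%**

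Exact enumeration of the uncorrected chi-square test gives 80.7% at 54 per arm and 79.3% at 52. Both methods put the cost at about 1.5 points.

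**The case against.** The strongest reply is that this hardly matters. The gap is five or six randomised infants and about 1.5 points of power, set against a 20% loss rate that is itself a round planning figure. If actual loss stays below 17%, nothing is lost. That argument stands, and it is why the point is minor. It does not make the three figures agree.

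Three stronger readings may tempt a reader. The article does not support them.

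- **That investigator-decided loss contradicts intention-to-treat.** Section 2.12 names the investigator's decision, beside parental withdrawal, only as an expected cause of loss when planning numbers. Allowing for missing outcomes is compatible with intention-to-treat, and nowhere does the article say that such infants leave the analysis. Grounds for withdrawal and the handling of missing outcomes are details that an article may leave to the full protocol or SAP. Nor is the 20% a permitted quota of investigator removals: it is a planning assumption that also covers parental withdrawal.
- **That the exclusion criteria invite removal after randomisation.** Section 2.4 lists "infants with genetic disorders (diagnosed before and after birth) deemed incompatible with survival, and infants with diagnosed cholestasis". But Section 2.6 places screening for these criteria within enrolment, and Table 1 marks them only in the enrolment column. Enrolment itself takes place after birth, so a postnatal diagnosis can precede randomisation.
- **That power falls to about 72%.** Fisher's exact test gives 72.2% at 52 per arm, but it gives only 74.7% at the full 54. Most of that deficit comes from the choice of test. The inflation accounts for about 2.5 points of it.

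**Conclusion.** The target is wrong as written, and the error is minor. On the plan's own figures, 20% loss calls for 135 infants (136 for equal arms). The stated 130 leaves 104 evaluable infants and 78.5% power in place of 80.1%, and it meets the requirement of 108 only up to 16.9% loss.

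The inflation error itself depends on nothing beyond the 108 and the 20%. The power figures assume a two-sided test, an absolute 25-point difference from 80%, equal loss in the two arms, and the pooled normal approximation that reproduces the 54. They do not change if the same difference is taken from 45% to 20%, because those rates mirror 55% and 80% around one half. The finding is confined to the arithmetic of Section 2.12 and implies nothing about bias or the analysis population.

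**What to change.** Either of two changes to Section 2.12 settles it.

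1. **Keep 130 and restate what it buys**, for example: *130 randomised infants give 80% power with up to about 17% loss; at 20% loss (104 evaluable) power is about 78.5%.* This costs one sentence.
2. **Correct the target to 136** (68 per arm), if the sponsor prefers to keep 80% power at 20% loss. Then 136 × 0.8 = 108.8, which meets the required 108. This costs six more infants and their mothers. Section 2.2 gives an average of 80 births a year below 33 weeks, so about 240 over three years. The target would rise from 54% (130/240) to 57% (136/240) of them.

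The first is sufficient. The second is the cleaner choice if recruitment allows.
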